### Sample Size Calculation

Similar interventions in other subject domains have been found to have an mean effect size of 0.22 (95% CI 0.16-0.27) from a meta-analytic fixed-effects model [24]. To detect an effect size of 0.22 with a two-sided 5% significance level and a power of 80%, a sample size of 83 participants per group, who reach the primary endpoint of the study, is necessary. A sample size calculation for a one-way ANOVA, together with one-sample and paired-sample *t* test analysis using the same effect, power, and significance parameters produce the same required sample size. We anticipate recruiting this number of participants (N=166) in 6 months. The sample size calculation formula is given in the Multimedia Appendix 1.

Based on the alpha and beta tests of the LIFE version, we are assuming a 50% dropout rate of study participants, with drop-out defined as the incomplete or single use of the LIFE smartphone app. We plan to recruit at least 332 participants to account for this dropout rate. To encourage repeated usage of LIFE, participants will receive up to three email reminders from the time they are enrolled into the study, spread over 3 weeks. Demographic data will be collected in the app during its initial use by study participants at the end of the first learning session. Thus, for learners who drop out before completing the first session, or chose not to fill in those data, no demographic data will be available. Logistic regression analyses will be performed on these data to evaluate whether there is a systematic bias caused by attrition of study participants that affects the interaction between the study groups and performance, exposure to previous ETAT+ training, clinical cadre, age of participant, and level of experience. In an effort to ensure participant recruitment is at par with the required study sample size, a monthly target of 30 participants, evaluated at the end of each month, has been set for this study.

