### Statistical Methods and Planned Analysis

For the primary endpoint, we will use the Morris G effect size to analyze the differences among group means in the study population. This will be assessed after the performance from the second round of training through the mobile app has been recorded. Secondary analysis will be conducted using regression analysis, with learning gains as the dependent variable and the aforementioned secondary outcomes as the independent variables, to evaluate their effect on learning gains. Learning gains, defined as the amount the health care providers learned divided by the amount they could have learned [40], will be calculated with the formula given in Equation 8 in Multimedia Appendix 1.

Due to the definition of the primary learning outcome used in this study, the outcome cannot be computed for study participants whose dropout is characterized by the lack of at least two complete learning sessions. Without a postbaseline assessment, “intention-to-treat” analysis cannot be performed for dropout cases unless we impute outcomes, which tends to produce biased estimates [41]. This study will not be able to conduct an intention-to-treat analysis. However, dropout numbers will be reported in relation to those who reached the study’s primary endpoint, and their implications will be discussed with regard to self-regulated self-directed learning [37-39].

Qualitative interviews will be conducted in parallel with the experiment for participants who have reached the primary endpoint and those who drop out. These interviews will be used to explore how self-regulation in learning affected the use of the smartphone-based learning platform and to provide context for interpreting the observed learning outcomes from this study apart from offering evidence for tool validation.

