## Results

This project was funded in November 2016. Data were collected from February 2019 up to July 2019. As of July 2019, we enrolled 541 participants, of whom 238 reached the primary endpoint, with a further 19 qualitative interviews conducted to support evaluation (New-Born Unit in-charge nurses, n=4; Paediatric Intensive Care Unit nurses, n=5, final-year medical students already doing clinical rotations, n=4; and student clinical officers and nurses already doing clinical rotations, n=6). Full analysis will be conducted once the number of required participants is met, and the results are expected to be published by Spring of 2020.

Based on the education literature [24,44,45], an effect size of approximately 0.2, 0.5, and 0.8 will be considered small, moderate, and large, respectively. These thresholds represent the magnitude of effect and reflect our assumption that a statistically significant result is not necessarily important or meaningful; for example, for an effect size of 0.2, the difference between the study groups is trivial even if it is statistically significant [44,46].

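### The attrition-bias regression excludes randomised learners who leave during session 1 or skip the form, so it can speak only to later loss

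*Protocol article*

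**What the plan says.** All from the protocol article.

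- **Sample Size Calculation, definition and assumed rate.** The article writes "we are assuming a 50% dropout rate of study participants", "with drop-out defined as the incomplete or single use of the LIFE smartphone app". Someone who abandons session 1 and someone who completes one session and never returns are both dropouts.
- **Sample Size Calculation, covariates.** Demographics are entered in the app when the first session is finished. The article states that "for learners who drop out before completing the first session, or chose not to fill in those data, no demographic data will be available".
- **Sample Size Calculation, attrition check.** The next sentence reads "Logistic regression analyses will be performed on these data to evaluate whether there is a systematic bias caused by attrition of study participants". It names study group, performance, earlier ETAT+ training, cadre, age and experience as the variables of interest.
- **Study Design; Randomization.** Allocation happens when the app is first launched, before session 1 and before the form.
- **Intervention.** Feedback differs by arm from the incorrect attempts onwards. Performance scores are issued only once a session has been completed.
- **Statistical Methods and Planned Analysis.** "This study will not be able to conduct an intention-to-treat analysis". Dropout numbers will be reported against those who reached the endpoint, and interviews will include people who dropped out. A comparison of dropout by arm is not stated.
- **Results.** "we enrolled 541 participants, of whom 238 reached the primary endpoint".

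**The concern.** The regression is meant to evaluate selection caused by attrition, but a participant enters it only by finishing session 1 and filling in the form. Both events follow randomisation and exposure to the allocated feedback. If one style of feedback makes people give up sooner, some of that loss would fall inside session 1, where this model has no data.

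This matters because the primary analysis uses only people with two complete sessions and the article rules out intention to treat. The comparison then depends on the two arms' completers being alike. A regression that shows no pattern could be read as support for that assumption while saying nothing about the first stage of loss.

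**Working it through.** **1. The plan's own figure.** Completers needed: 83 × 2 = 166. With 50% dropout, 166 / (1 − 0.50) = 332. This reproduces the recruitment target ("We plan to recruit at least 332 participants to account for this dropout rate") and implies 166 planned dropouts.

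**2. Who can have a row in the regression.**

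| Participant | Randomised | Dropout as defined | Session 1 score | Demographics | In the regression |
|---|---|---|---|---|---|
| Leaves during session 1 | yes | yes | no | no | no |
| Finishes session 1, skips form, does not return | yes | yes | yes | no | no |
| Finishes session 1 with form, does not return | yes | yes | yes | yes | yes |
| Finishes two sessions, with form | yes | no | yes | yes | yes |
| Finishes two sessions, no form | yes | no | yes | no | no |

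The only contrast left is row 3 against row 4.

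**3. Count at July 2019.** 541 − 238 = 303 not yet at the endpoint; 303 / 541 = 56.0%. The Abstract dates this count 18 July, with recruitment open until 31 July, so 303 is not a final number of dropouts.

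**4. How many are excluded.** Let f be the share of dropouts who leave before the end of session 1 or do not fill in the form. The documents do not give f. The values below are assumptions, and for simplicity all completers are taken to have a form.

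Excluded = dropouts × f. Apparent dropout among those analysed = dropouts × (1 − f) / [dropouts × (1 − f) + completers].

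| f (assumed) | Planned: excluded of 166 | Apparent dropout (true 50%) | July 2019: excluded of 303 | Apparent dropout (56% at that count) |
|---|---|---|---|---|
| 25% | 42 | 43% | 76 | 49% |
| 50% | 83 | 33% | 152 | 39% |
| 75% | 124 | 20% | 227 | 24% |

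The table shows how the result depends on f. It does not estimate f.

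**5. What a comparison by arm could detect.** It needs only allocation and completion status. Take 541 / 2 ≈ 270 per arm, two-sided 5%, normal approximation: power = Φ(|p1 − p2| / SE − 1.96), with SE = √[(p1(1 − p1) + p2(1 − p2)) / 270].

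- 38% v 50%: SE = √[(0.2356 + 0.2500) / 270] = 0.0424; 0.12 / 0.0424 = 2.83; power about 0.80.
- 40% v 48%: SE = √[(0.2400 + 0.2496) / 270] = 0.0426; 0.08 / 0.0426 = 1.88; power about 0.47.

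At the observed overall completion of 238 / 541 = 44%, the 95% interval for the difference has half-width 1.96 × √(2 × 0.44 × 0.56 / 270) = 0.084, or about 8 percentage points either side.

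**The case against.** - **The gap is disclosed.** The sentence just before the regression tells the reader who will lack demographics, and nowhere does the article promise a finding of no bias for everyone randomised. This stands, and there is no concealment. But disclosing the gap does not bring these people into the model, and the stated purpose of the regression carries no matching restriction.
- **Dropout will be reported anyway, and interviews are planned.** True, so the regression is not the only information on attrition. The counts are promised against completers, with no comparison by arm stated, and interviews cannot measure differential loss.
- **An article may leave detail to a fuller document.** That would answer a complaint about missing model specification. Here the article does state the method and its data source, and the limitation follows from those statements.
- **The number excluded is unknown.** This stands. A reader might infer that most dropouts are invisible to the model. The documents do not support that: incomplete and single use are not separated, and some of the 303 might still have finished. Nor is enrolment defined precisely enough to be sure that every early leaver is among the 541.
- **Adding early leavers brings in people of unverified eligibility.** This also stands. The app is public, non-health workers and retirees are excluded, and cadre may be unknown without the form.

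**Conclusion.** The point holds on the article's own wording: the planned regression cannot examine loss during session 1 or among people without a form, although the definition of drop-out includes early leavers and feedback already differs by arm at that stage. Its conclusions reach only loss between finishing session 1 with a form and finishing session 2.

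The size of the exclusion cannot be computed. At most it concerns some part of the 303 (56%) not at the endpoint in July 2019, or of the 166 dropouts planned for.

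A reader might go further and infer that the treatment effect is biased by some amount. The documents do not support this. They give no completion by arm, no split of dropout by stage, and no link between staying and learning gain, and a difference in overall completion could arise entirely after session 1. The defect is a check with limited reach, not demonstrated bias.

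The point assumes that the regression uses the demographic covariates listed, so that a participant without them contributes nothing. It is worth correcting because the remedy is cheap and the full analysis had not been run.

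**What to change.** Before the full analysis:

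1. **Primary attrition check.** Compare by arm the proportion reaching the primary endpoint among all randomised enrolled participants, excluding only those known to be ineligible. Report the difference with a 95% confidence interval.
2. **Optional predictor.** Add first-task performance only where data from unfinished sessions were synchronised. The article does not establish that they were.
3. **Demographic regression.** Keep it as a second step, and state that its conclusion applies to session 1 finishers who filled in the form.
4. **Interpretation.** State in advance that a non-significant difference by arm will not be read as absence of bias. Similar completion proportions would also not show that the same kinds of people stayed in each arm.

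**Cost.** A little more analysis, needing only allocation and completion status for step 1. The comparison will include some participants of unverified eligibility, which should be stated. Power is limited, as shown above.

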### Randomization

For allocation of the participants, an in-app algorithm will randomly generate a value of zero or one when the Android-based smartphone app is launched for the first time. This will determine whether the participant is allocated to the control or experiment group. It will also blind both the study participants and intervention staff to the group allocation of participants during the experiment, but not at the analysis stage. Sequence generation for random allocation is a computerized procedure pegged on a single instance (ie, smartphone app installation) that mimics a coin-tossing procedure. Therefore, use of permuted blocks of random sizes to assign participants to either the control or experimental group is not possible and will not be implemented.

### Statistical Methods and Planned Analysis

For the primary endpoint, we will use the Morris G effect size to analyze the differences among group means in the study population. This will be assessed after the performance from the second round of training through the mobile app has been recorded. Secondary analysis will be conducted using regression analysis, with learning gains as the dependent variable and the aforementioned secondary outcomes as the independent variables, to evaluate their effect on learning gains. Learning gains, defined as the amount the health care providers learned divided by the amount they could have learned [40], will be calculated with the formula given in Equation 8 in Multimedia Appendix 1.

Due to the definition of the primary learning outcome used in this study, the outcome cannot be computed for study participants whose dropout is characterized by the lack of at least two complete learning sessions. Without a postbaseline assessment, “intention-to-treat” analysis cannot be performed for dropout cases unless we impute outcomes, which tends to produce biased estimates [41]. This study will not be able to conduct an intention-to-treat analysis. However, dropout numbers will be reported in relation to those who reached the study’s primary endpoint, and their implications will be discussed with regard to self-regulated self-directed learning [37-39].

Qualitative interviews will be conducted in parallel with the experiment for participants who have reached the primary endpoint and those who drop out. These interviews will be used to explore how self-regulation in learning affected the use of the smartphone-based learning platform and to provide context for interpreting the observed learning outcomes from this study apart from offering evidence for tool validation.

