## Methods

### Study Design

The study (trial registration: Pan African Clinical Trials Registry PACTR201901783811130) will have a parallel-group double-blinded randomized experiment design with an allocation ratio of 1:1. The participants will be randomized to the intervention or control group when they launch the android-based training app for the first time on their individual smartphone devices.

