### Intervention

The intervention in this study involves adaptive, personalized, and immediate feedback that is provided while learning through a smartphone-based serious gaming Android app. The content to be learned is based on ETAT+ guidelines, a course that is already offered in nine low-income countries [7,8,10]. The intervention will be available on the Google Play Store where it will be publicly accessible, downloadable, and installable to any compatible android-based mobile device. All study participants will receive a link to the mobile app hosted on the Android Play Store. The LIFE app was designed for Android’s Target SDK 19 as the minimum version of Android supported as of February 2019 (which targets 100% of Android devices) [29]. Given that the intervention has undergone alpha and beta testing on health care providers’ smartphones since October 2017 in Kenya, we are confident of the stability of the app.

The personalized immediate feedback to be given to the experimental group participants is designed to arouse meaningful immersive learning experiences from continuous interaction between the learners and the smartphone-based training [30,31]. This adaptive feedback will be provided to experiment group participants after each incorrect attempt at a learning task with three cascading detail levels based on predicted probability that the learner’s next attempt is going to be correct. The wording of the feedback provided is dependent on the number of incorrect choices the learner had selected and the actual incorrect choices themselves. The control group study participants will receive standardized nonpersonalized immediate feedback after each incorrect attempt at a learning task, with the feedback on the first incorrect attempt asking the learner to retry and the feedback on the second attempt providing a detailed explanation of the correct choices to select.

The LIFE app is a measurement tool; at the end of successful completion of a learning session, the platform provides performance scores based on whether each learner’s response to the learning task was correct on the first attempt.

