### Outcomes

The primary endpoint for both arms of the experiment will be the presence of two complete rounds of learning sessions using LIFE, the former is the pretest round and the latter is the posttest round. Both scores will be converted into percentages. From the pre-post scores, the study’s main outcome—the learning effect size (*d*), [35]—will be calculated as follows:

where the pooled SD is defined as:

The bias adjustment is provided by the formula:

where *n*_*T*
_ is the sample size of the treatment group, *M*_*pre,T*
_ is the pretest mean for the treatment group, *M*_*post,T*
_ is the posttest mean for the treatment group, *SD*_*pre,T*
_ is the SD of means for pretest in the treatment group, *SD*_*post,T*
_ is the SD of means for posttest in the treatment group, *n*_*C*
_ is the sample size of the control group, *M*_*pre,C*
_ is the pretest mean for the control group, *M*_*post,C*
_ is the posttest mean for the control group, *SD*_*pre,C*
_ is the SD of means for pretest in the control group, and *SD*_*post,C*
_ is the SD of means for posttest in the control group.

The effect size from equation from (1) is referred to as *Morris G* [35] and represents the mean difference between the study groups. Because of randomization, this calculation allows to control for pre-existing differences among learners (eg, intelligence quotient level), to estimate treatment effectiveness even when the treatment and control groups are not equivalent, and to consider the variances of both pretest and posttest scores. This contrasts with other forms of effect-size calculation such as Hedges G and Becker D, which only use pretest or pooled variances [35]. In this model, the pretest and posttest variances are assumed to be homogeneous.

Secondary outcomes that will be assessed are time difference between each round of learning sessions, the number of times a learner has encountered a learning task up to the current opportunity (ie, cumulative attempts on learning task per learner), the time spent on each learning task, and the level of feedback provided. These calculations will be performed in Python, version 3.6.8 (Python Software Foundation, Wilmington, DE).

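### The secondary regression reads effects from post-randomization variables, two of which arise wholly or partly from the errors that determine the learning gain

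*Protocol article*

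**What the plan says.** Statistical Methods and Planned Analysis specifies a regression "with learning gains as the dependent variable and the aforementioned secondary outcomes as the independent variables, to evaluate their effect on learning gains". The same section defines the gain in words, as what was learned relative to what could have been learned. The formula is Equation 8 of an appendix that is not shown.

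The regressors come from the Outcomes section. It calls them secondary outcomes and lists "time difference between each round of learning sessions, the number of times a learner has encountered a learning task up to the current opportunity" (glossed there as cumulative attempts), then "the time spent on each learning task, and the level of feedback provided".

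Three other statements matter:

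- **Timing of allocation** (Study Design): participants are "randomized to the intervention or control group when they launch the android-based training app for the first time".
- **What triggers feedback** (Intervention): "This adaptive feedback will be provided to experiment group participants after each incorrect attempt at a learning task with three cascading detail levels". The level is set by the predicted probability that the next attempt will be correct. Control participants also get feedback after each incorrect attempt, as a fixed sequence: a retry prompt, then a full explanation.
- **What is scored** (Intervention): whether the response to each task was right at the first attempt.

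**The concern.** The stated purpose of the regression is causal, but none of its four regressors is randomized. All of them arise after allocation.

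For feedback level and attempts the problem goes beyond confounding. A wrong first attempt reduces the round's score, triggers feedback and usually leads to another attempt. The gain is then computed from the two scores. Regressor and outcome therefore share the same errors, and a slope away from zero is expected even if feedback teaches nothing. In the experimental arm the level also follows the app's own prediction of performance, so it partly measures ability. Because one arm has three adaptive levels and the other a fixed two-step sequence, feedback level is also close to being the treatment itself.

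The trial asks whether a form of feedback improves learning. A reported effect of feedback level would be taken as direct evidence on that question, although its sign could depend on which round's feedback was counted.

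**Working it through.** The plan gives no figure to reproduce. The check has two parts.

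**1. From the definitions.** Read the verbal definition of gain as G = (post − pre)/(100 − pre). This is an assumption, because Equation 8 is not shown. Let E1 and E2 be the proportions of tasks wrong at the first attempt in rounds 1 and 2. With scores in percent, 100 − pre = 100·E1 and post − pre = 100·(E1 − E2). Hence

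G = (E1 − E2)/E1 = 1 − E2/E1.

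Each first-attempt error is also a feedback episode, so these counts determine the gain:

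- **Round 2:** ∂G/∂E2 = −1/E1, always negative. More posttest errors mean more feedback and less gain.
- **Round 1:** ∂G/∂E1 = E2/E1², positive with E2 held fixed. Across learners, however, E2 rises with E1. If everyone improves equally on the logit scale, weaker learners remove a smaller share of their errors, which pulls the slope down. The net sign depends on how noisy the pretest score is, and so on the number of tasks.

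**2. Simulation with no effect of feedback or attempts.** The 166 completers come from Sample Size Calculation. All other inputs are assumptions: a logistic ability model with SD 0.8, the same practice shift for every learner, and a range of task numbers.

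The first run used a shift of 0.6 logit, a 50% chance that an error leads to a second one, an arm term in the model, and 1,000 runs per cell. Entries are mean slope and percentage of runs with p < 0.05:

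| Feedback counted | 10 tasks | 20 tasks | 40 tasks |
|---|---|---|---|
| Round 1 | +0.48 (96%) | +0.25 (69%) | +0.01 (15%) |
| Round 2 | −0.73 (100%) | −0.51 (99.6%) | −0.41 (98%) |
| Both rounds | −0.07 (18%) | −0.07 (38%) | −0.10 (78%) |

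A second run, set up slightly differently, covered 10 to 60 tasks and shifts of 0.3 to 1.0 logit. Significant slopes occurred in:

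- about 17–100% of runs for round-1 feedback;
- 82–100% for round-2 feedback, with negative slopes;
- 6–96% for both rounds combined.

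The round-1 sign reversed within that grid. At 60 tasks and a shift of 1.0, about 61% of runs were significant and 95% of slopes were negative. The nominal rate is 5% throughout.

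**Limits of the simulation.** It counts feedback episodes, whereas the protocol's variable is the level of feedback, and it omits the other regressors. It shows that the shared-error mechanism is enough to create a slope. It does not reproduce the planned model.

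**The case against.** **The mechanism does not cover every regressor.** A reader might infer that all four variables are products of error. The text does not support that. Time between rounds is self-paced and prompted by reminders, and time on task is not generated by mistakes. Attempts are defined by encounters with a task, which may include voluntary replay. This objection stands: the shared-error argument applies to feedback level and only partly to attempts. The other two are still post-randomization, so they too lack the protection of randomization.

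**Silence is not omission.** A reader might infer that the secondary outcomes will never be compared between arms, or that arm and pretest score are left out of the model. The article says neither. Between-arm summaries and covariate lists are commonly left to a full protocol or analysis plan. This also stands, and the point does not rely on it. What the article does state is the dependent variable, the independent variables and the causal purpose.

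**The percentages rest on invented inputs.** They do. A single setting, such as 25 tasks with a 0.6 logit shift, gives about 60% for round 1 and 26% for both rounds. It would be wrong to quote these as the error rate of this trial. Only the ranges are informative. The negative round-2 slope depends least on the inputs, because it follows from the definitions.

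**It is one sentence about a secondary analysis.** True, but that sentence fixes how the coefficients are to be interpreted, on the very topic the trial studies.

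**Conclusion.** The concern holds in this form: the coefficients for feedback level and cumulative attempts cannot be read as effects on learning gain. Errors enter both sides of the regression, and feedback level differs by arm by design. With no true effect, rejection ran from just above the nominal 5% to 100%, depending on the round counted and the assumed inputs. The round-1 sign was not stable.

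This rests on the usual reading of the verbal definition of gain and on the scoring and feedback rules in the Intervention section. The numerical ranges also rest on the assumed task numbers, ability spread and practice shift. For time between rounds and time on task, the conclusion is only that a causal reading is not protected by randomization.

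A reader might infer that the main result is compromised as well. It is not: the primary Morris G comparison does not use these regressors.

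**What to change.** In Statistical Methods and Planned Analysis:

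1. Replace the stated purpose of evaluating effects with an exploratory analysis of association.
2. Use only exposures measured in round 1, before the posttest. Adjust for pretest score and fit the model within each arm. Omit any exposure that is an exact function of the pretest score, such as a count of first-attempt errors, because it is collinear with that score and the model cannot be fitted.
3. State that no arm coefficient will be interpreted from a model containing these variables.
4. Report time between rounds, attempts and time on task by randomized arm with 95% confidence intervals. Say that time between rounds exists only for learners who completed two rounds, so that comparison is restricted to completers.
5. Describe feedback level within arm only, because its scale differs between arms.

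The cost is a change of analysis wording and a weaker, non-causal secondary claim. No new data are needed.

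### The secondary regression reads attempts and feedback as causes of learning gains, although retries and feedback follow wrong answers in the same rounds that produce the gains

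*Protocol article*

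**What the plan says.** All references are to the Methods of the protocol article.

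- **Score (Intervention).** At the end of a session the app gives "performance scores based on whether each learner’s response to the learning task was correct on the first attempt".
- **Rounds (Outcomes).** The primary endpoint is "the presence of two complete rounds of learning sessions using LIFE, the former is the pretest round and the latter is the posttest round". The two test rounds are thus also the learning rounds.
- **Feedback trigger (Intervention).** In both arms feedback appears once a learner has answered a task incorrectly. In the control arm its content is fixed by the attempt number. In the adaptive arm its level follows the predicted chance that the next attempt will be right.
- **Secondary outcomes (Outcomes).** These are the time between rounds, "the number of times a learner has encountered a learning task up to the current opportunity" (glossed as "cumulative attempts on learning task per learner"), "the time spent on each learning task, and the level of feedback provided".
- **Secondary analysis (Statistical Methods and Planned Analysis).** A regression "with learning gains as the dependent variable and the aforementioned secondary outcomes as the independent variables, to evaluate their effect on learning gains". Learning gains are "defined as the amount the health care providers learned divided by the amount they could have learned".

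The section gives no restriction of the predictors to one round and no caution that the relation is only an association.

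**The concern.** A wrong first answer in round 2 does two things at once: it lowers the posttest, and it triggers feedback and a retry. That part of the predictor is produced by the outcome. A wrong first answer in round 1 likewise lowers the pretest, which enters the gain, and adds a retry and feedback. A relation between gain and attempts or feedback can therefore appear inside each arm even if neither has any influence on learning. Adding study arm to the model would not remove it.

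At stake is the reading of the secondary results. A coefficient labelled as an effect could suggest that more feedback or more practice harms learning, or helps it, when it reflects how the variables are built. In a trial about feedback, readers are likely to take such a coefficient seriously.

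**Working it through.** The protocol states no figure for this analysis, so there is none to reproduce. The mechanism is shown first by arithmetic, then by simulation.

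**Assumption on the gain.** Equation 8 in Multimedia Appendix 1 is not shown. From the verbal definition I take gain = (post − pre) / (100 − pre). The round-2 coupling arises for any gain that rises with the posttest.

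**One learner, 20 tasks (assumed).** Each further first-attempt error moves a score by 100/20 = 5 points and adds at least one retry.

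| Case | Pre | Post | Gain | Change in attempts |
|---|---|---|---|---|
| Reference | 50 | 70 | 20/50 = 0.40 | – |
| One more round-2 error | 50 | 65 | 15/50 = 0.30 | at least +1 |
| One more round-1 error | 45 | 70 | 25/55 = 0.45 | at least +1 |
| One more error in each | 45 | 65 | 20/55 = 0.36 | at least +2 |

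The same rise in attempts goes with a lower gain or a higher gain, according to the round in which the error fell.

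**Null simulation.** There are 166 learners (83 per group, from Sample Size Calculation). Assumed: 15 or 30 tasks; mean baseline logit 0; ability SD 0, 0.5 or 1 on the logit scale; the same 0.5-logit improvement for everyone; one retry after a wrong first attempt, with a second retry 30% of the time. Attempts have no effect by construction. Gain is regressed on standardised attempts plus arm, with 400 data sets per setting. Cells give the mean correlation of attempts with gain and the share of data sets with p < 0.05 for attempts (nominal 5%).

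| Tasks | Ability SD | Round 1 only | Round 2 only | Both rounds summed |
|---|---|---|---|---|
| 15 | 0 | +0.55; 100% | −0.62; 100% | −0.02; 10% |
| 15 | 0.5 | +0.38; 99.8% | −0.46; 100% | −0.03; 11% |
| 15 | 1.0 | +0.18; 69% | −0.35; 99% | −0.09; 26% |
| 30 | 0 | +0.55; 100% | −0.68; 100% | −0.07; 12% |
| 30 | 0.5 | +0.26; 86% | −0.50; 99.5% | −0.12; 34% |
| 30 | 1.0 | +0.07; 29% | −0.35; 94% | −0.15; 50% |

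**Sensitivity to the assumptions.** A second set of runs used 238 learners (the number reported in Results as having reached the endpoint), with these assumptions: 10, 20 or 40 tasks; baseline logit 0 to 1; ability SD 0.5 or 1; a uniform 1-logit improvement; retries right 60% of the time. Round-2 events correlated −0.37 to −0.61 with gain and were significant in essentially all data sets. Cumulative events were significant in 10% to 99%. Round-1 events ranged from −0.22 to +0.28, so their sign also changes with the scenario. Further null runs with 238 learners gave 20% to 100% for cumulative events and 98% to 100% for round 2.

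**Check of the remedy under the null.** The posttest is regressed on round-1 events and pretest. If retry success is the same 60% for every learner, the round-1 coefficient is significant in 2% to 8% of data sets, close to nominal. If retry success rises with ability, it is significant in 81% to 92% in one set of runs and 96% to 100% in another. The pretest measures ability imperfectly, the number of retries carries further information on ability, and ability also drives the posttest.

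**The case against.** Several objections have force.

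- **The variables are not the score in another form.** The first attempt at each task happens whatever the answer, retries per missed task vary, and adaptive feedback level follows a prediction. A reader might infer that attempts and feedback merely restate the score, or that the regression can return nothing but an artefact. The protocol does not support that. Feedback level also differs by randomised arm, so a coefficient may contain real signal. What stands is that the planned model cannot separate that signal from the coupling.
- **The attempt count may be a running count.** The phrase about the current opportunity can be read as covering only what came before a given response. The gloss as cumulative attempts per learner leaves this open, and nothing similar limits feedback level or time on task. Even the narrower reading leaves the round-1 coupling.
- **A condensed article leaves model detail elsewhere.** Lag, unit of analysis and covariates may be set in a fuller document, and their absence alone would be no finding. But the article does state the dependent variable, the independent variables and the aim of estimating an effect, and that combination is the problem.
- **The simulations are not the planned model.** They use counts of attempts or feedback events, not feedback level, and not the full set of predictors. The rates vary widely and the near-100% figures are for round 2 alone, a predictor the protocol does not name. They illustrate direction and possible size; they do not predict this trial's error rate.
- **Consequences.** A reader might infer that this regression decides which app features are kept. No section says so; the remark on feature inclusion under Intervention concerns A/B experimentation in general.

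**Conclusion.** The concern holds for extra attempts and feedback, and partly for time on task. It does not apply to the interval between rounds. As stated, the secondary regression cannot support a reading as effects: round-2 retries and feedback partly result from the posttest, and round-1 ones are tied to the pretest. With no true effect, the cumulative count was significant in about 10% to 100% of simulated data sets against a nominal 5%, with size and sign depending on the round counted. That range rests on assumed task number, ability spread, improvement and retry success, and on the assumed form of the gain.

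The primary Morris G comparison between arms does not use these predictors and is unaffected. The plan should be corrected, but the main result is not in doubt on this account. A reader might also infer that restricting predictors to round 1 and adjusting for pretest makes a causal reading safe. It does not: confounding by learner ability remains.

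**What to change.** In Statistical Methods and Planned Analysis (and in the analysis plan, if there is one), replace the sentence on the secondary regression with wording such as:

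> Secondary regression will describe the association of round-1 attempts, round-1 time on task, round-1 feedback level and the interval between rounds with the posttest percentage, with pretest percentage and study arm as covariates. Learning gains will be reported as a descriptive supplement. Using predictors recorded before the posttest round avoids reverse causation but does not remove confounding by learner ability; coefficients will not be interpreted as effects of attempts, time or feedback.

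The change from effect to association is the essential part; the model changes do not replace it.

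Cost: no new data are needed, provided the app's records identify the round. The dependent variable of a protocol-defined secondary analysis changes after 238 participants had reached the endpoint, so the change should be dated and recorded as an amendment before the analysis is run. Some apparent associations may weaken or disappear. Round-1 events and pretest are strongly collinear (correlation roughly −0.7 to −0.95 in the simulations), so the estimates will be imprecise.
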